## Abstract

**Objectives:**

Timely diagnosis remains a challenge in axial SpA (axSpA). In addition, data are scarce on the impact of diagnostic delay and disease progression in affected individuals. The British Axial Spondyloarthritis Inception Cohort (BAxSIC) study aims to investigate the impact of newly diagnosed axSpA, the natural history of the disease and the effect of diagnostic delay on disease outcomes.

**Methods:**

BAxSIC is a prospective, multicentre, observational study. Eligible participants are adults (≥16 years of age), with a physician-confirmed diagnosis of axSpA in the 6 months prior to study entry, recruited from secondary and tertiary rheumatology centres in the UK. Participants will be followed up for 3 years, with in-person visits at baseline and 24 months. In addition, patient self-reported assessments will be recorded remotely via the online electronic case report form (eCRF) at 6, 12, 18, 30 and 36 months.

**Results:**

The first patient was enrolled in BAxSIC in June 2023. Recruitment is currently ongoing and is planned to end in June 2026. Initial results will be available in 2027. Since opening, the trial has undergone two protocol amendments.

**Conclusion:**

The BAxSIC study is the first inception cohort designed to investigate the impact of diagnostic delay on clinical presentation and long-term functional outcomes in patients with axSpA in the UK. With an innovative, patient-led virtual longitudinal data collection model, data generated from this study will help inform and improve the care of people newly diagnosed with axSpA.

**Trial registration:**

ClinicalTrials.gov (http://clinicaltrials.gov), NCT05676775.

Key messagesBAxSIC is a large UK-based inception cohort of newly diagnosed axSpA patients utilising virtual follow-up.BAxSIC aims to investigate the impact of diagnostic delay in axSpA and long-term functional outcomes.

## Introduction

Axial SpA (axSpA) is a chronic, immune-mediated condition characterized by inflammation in the axial skeleton and associated with extramusculoskeletal manifestations (EMMs). In the UK, an estimated 220 000 people live with axSpA, with a prevalence of 0.3–1.2% depending on the definition utilized [1]. The prototypic phenotype formerly known as AS is defined by the presence of new bone formation, leading to fusion in the spine and SI joints detected on radiographs [radiographic axSpA (r-axSpA)], which often manifests late in the disease course and not in all patients with axSpA. The advent of MRI at the turn of this century facilitated earlier diagnosis, prior to the development of new bone in the spine and SI joints and in those in whom new bone formation does not occur [non-radiographic (nr-axSpA)]. In parallel with these diagnostic advances, the development of biologic and targeted synthetic DMARDs (bDMARDs and tsDMARDs) have greatly improved quality of life and function in people with axSpA by improving symptoms of back pain, fatigue and stiffness [2]. However, their impact on disease progression and long-term outcomes is less clear [3].

Diagnostic delay is common in axSpA [4], and is worse in females than males [5]. In the UK, a recent report from the National Axial Spondyloarthritis Society (NASS) highlighted a mean time from symptom onset to diagnosis of 8.5 years [6]. Causes of diagnostic delay in axSpA are multifactorial and include the insidious onset of the disease, poor public and healthcare worker awareness, the absence of diagnostic serum biomarkers [7] and the reliance on clinician diagnosis based on the history, imaging and laboratory findings. The impact of this delay on patients is poorly researched, with a few small-scale studies primarily focusing on male patients with r-axSpA [8]. A recent study showed a higher burden of disease with the development of uveitis and inflammatory bowel disease associated with longer diagnostic delay [9]. Further research into the impact of diagnostic delay on the individual’s initial presentation and on the wider axSpA population is therefore vital to improving patient care and outcomes.

Hypothesizing that diagnostic delay leads to worse long-term functional outcomes and affects the overall disease course of axSpA, we aimed to assess the impact of diagnostic delay on clinical presentation and long-term outcomes, including work participation, quality of life and function in axSpA.

## Methods

### Study design

The BAxSIC study (https://baxsic.uk) is a prospective inception cohort study (Supplementary material, available at *Rheumatology Advances in Practice* online) recruiting patients with newly diagnosed axSpA from secondary and tertiary rheumatology centres across the UK. The study protocol was developed by members of the Executive Committee of the British Society for Spondyloarthritis (BRITSpA, https://www.britspa.co.uk/), who are co-investigators for the study and members of the Trial Management Group (TMG). There is no minimum sample size required for the study due to the exploratory nature of the primary outcome.

### Study population

Patients are primarily recruited from rheumatology clinics. Eligible participants are consecutive patients who are ≥16 years of age with a diagnosis of axSpA made by a consultant rheumatologist within the 6 months prior to recruitment and able to give informed consent (Fig. 1). The exclusion criteria are age <16 years, unable to provide informed consent in English (despite efforts to facilitate informed consent through a Trust-appointed interpreter) or deemed in any other way to be unable to give informed consent. Recruitment to this study is based on a collaborative effort between multiple UK secondary and tertiary centres with the help of BRITSpA. Recruitment will last for 3 years with a total follow-up duration of 36 months (Fig. 1).

**Figure 1. rkae087-F1:**
[figure not shown]
Schematic diagram of the BAxSIC study assessments

### Baseline procedures

Consenting participants will attend an in-person baseline visit where data on date of onset of symptoms, date of confirmed diagnosis, sociodemographic characteristics, general health, family history and data relating to symptom onset and diagnosis date will be collected (Table 1). In addition, the following information available from routine medical records will be recorded: medication data including utilization of NSAIDs, conventional synthetic DMARDs, bDMARDs, tsDMARDs, analgesics and steroids. Laboratory data from HLA-B27 testing (ever) and CRP or ESR values available on the electronic health records for up to 6 months from diagnosis and thought to be related to axSpA in the opinion of the investigator will be recorded. Available imaging data from routine anteroposterior (AP) radiographs of the pelvis/SI joints and MRI of the SI joints and spine performed as part of routine clinical practice up to 12 months prior to study entry will be collected together with data from the report by local readers (either radiologist or rheumatologist) regarding the presence or absence of radiographic sacroiliitis in accordance with modified New York (mNY) criteria [10] or a positive MRI according to Assessment of SpondyloArthritis international Society (ASAS) definitions [11].

**Table 1. rkae087-T1:** Summary schedule of study assessments

Month ±28 days	0	6	12	18	24	30	36
Visit number	1	2	3	4	5	6	7

Clinician-/allied health professional–initiated assessments							
Full informed consent	X						
Confirmation of ongoing consent				X			
Inclusion/exclusion criteria	X						
Study ID/site	X						
NHS number 1	X						
Demographic data							
Sex	X						
Age at study entry	X						
Marital status	X						
Ethnic group	X						
Highest level of education attained	X						
Employment status	X			X			
Post code (for deprivation score)	X						
Alcohol intake (units per week)	X			X			
Smoking status (current, ex, never)	X			X			
History/symptoms							
Onset of back pain symptoms (date/duration of)	X						
Onset of other SpA-related symptoms (date/duration of)	X						
History/diagnosis							
Date of first rheumatology appointment	X						
Date of diagnosis (by consultant rheumatologist)	X						
Meets mNY criteria	X			X			
Meets ASAS criteria	X			X			
Relevant past medical history: psoriasis, psoriatic nail changes, uveitis, IBD, enthesitis, dactylitis, arthritis, costochondritis/date of onset	X			X			
Family history: AS, axSpA, psoriasis, IBD, inflammatory arthritis	X			X			
Relevant orthopaedic surgery (arthroplasty or spinal)	X			X			
Current evidence of: psoriasis, psoriatic nail changes, uveitis, IBD, enthesitis, dactylitis, arthritis, costochondritis/date of onset	X			X			
Events of special interest	X			X			
Medication (previous and current)							
NSAIDs	X			x			
DMARDs	X			X			
Other (including steroids, analgesics)	X			X			
Laboratory and imaging							
HLA-B27	X						
CRP (mg/l)	X			X			
ESR (mm/h)	X			X			
Imaging (SI joints X-ray/MRI)	X			X			
ASDAS-CRP	X			X			
Participant-initiated assessments							
Height (cm)	X			X			
Weight (kg)	X			X			
Events of special interest		X	X		X	X	X
Patient-reported outcomes							
Total spinal pain score	X	X	X	X	X	X	X
Patient global assessment of disease activity	X	X	X	X	X	X	X
BASDAI	X	X	X	X	X	X	X
BASFI	X	X	X	X	X	X	X
4D-AS questionnaire	X						
ASAS-HI	X	X	X	X	X	X	X
EQ-5D-5L	X	X	X	X	X	X	X
Work productivity and activity impairment and occupation	X	X	X	X	X	X	X
Anxiety and depression, PROMIS short form 4a	X	X	X	X	X	X	X
Fatigue, PROMIS short form fatigue 8a	X	X	X	X	X	X	X
Fibromyalgia, Wolfe questionnaire	X	X	X	X	X	X	X

The investigator will assess the current Axial Spondyloarthritis Disease Activity Score (ASDAS), determine whether the participant fulfils the mNY [10] or ASAS classification criteria [11] for axSpA and examine for any current evidence of psoriasis, uveitis, IBD, enthesitis, dactylitis, peripheral arthritis or costochondritis. Participants will complete questionnaires to assess function, work participation, disease activity, fatigue, comorbidities, overall health and quality of life (Table 2).

**Table 2. rkae087-T2:** Patient-reported outcome measures and questionnaires

Total spinal pain [20]
Patient global assessment of disease activity [21]
BASDAI [22]
BASFI [23]
4D-AS [24]
ASAS Health Index [25]
EuroQol 5 dimension, 5-level [26]
Work Productivity and Activity Impairment Questionnaire: Specific Health Problem (version 2.0) [27]
PROMIS Depression Short Form 4a [28]
PROMIS Anxiety Short Form 4a [29]
PROMIS Fatigue Short Form 8a [30]
Fibromyalgia, Wolfe questionnaire [31]

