### Follow-up procedures

At 6-month intervals (months 6, 12, 18, 30 and 36) participants will be asked to complete electronic data collection sheets and questionnaires (Table 2) via e-mail or text message. These will collect data regarding disease activity and EMMs in addition to patient-reported outcome measures. Participants will be sent up to three electronic reminders via the Research Electronic Data Capture (REDCap) system to complete each visit. Each visit will have a window of 28 days (±14 days). Participants may request paper versions, if required.

At 24 months (Fig. 1), participants will be invited for a further in-person review to collect data on medication use related to axSpA, employment status, alcohol and smoking status and comorbidities. Participants will be examined for any extra-axial features of SpA and data from routinely performed MRIs, X-rays and CRP/ESR will be collected. Patient reported outcomes and questionnaire data will also be collected at this visit (Table 2).

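### Baseline CRP/ESR is tied to the diagnosis date and filtered by investigator opinion, so the "current" baseline ASDAS-CRP can rest on a selected CRP taken up to 12 months before the visit

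*Protocol article*

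**What the plan says.** All from the Methods of the protocol article.

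- **Source.** Under Baseline procedures, laboratory and medication data come from routine care: "the following information available from routine medical records will be recorded".
- **Window and filter.** The laboratory values taken are "CRP or ESR values available on the electronic health records for up to 6 months from diagnosis and thought to be related to axSpA", and the relatedness test is applied "in the opinion of the investigator will be recorded". Whether the 6 months run before diagnosis, after it or both is not stated.
- **Entry.** Under Study population, participants need a "diagnosis of axSpA made by a consultant rheumatologist within the 6 months prior to recruitment".
- **Score.** After Table 1: "The investigator will assess the current Axial Spondyloarthritis Disease Activity Score (ASDAS". Table 1 marks CRP, ASDAS-CRP and the patient-reported scores at month 0.
- **Imaging, for comparison.** The imaging window is anchored to entry into the study: "performed as part of routine clinical practice up to 12 months prior to study entry".
- **Later in-person visit.** Under Follow-up procedures, at 24 months, "data from routinely performed MRIs, X-rays and CRP/ESR will be collected". The article gives no relatedness filter and no window there.
- **Treatment.** Table 1 records earlier and ongoing NSAIDs, DMARDs, steroids and analgesics at month 0, so some participants may already be on treatment at the visit.

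**The concern.** ASDAS-CRP combines symptom scores with a CRP and describes one moment only if the two are close in time. Here the symptom scores belong to the visit, while the CRP belongs to a period around diagnosis. Nothing in the article limits the gap between them, and treatment may start within it.

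The second problem is selection. The relatedness test decides whether a value enters the database at all. It is applied by site staff who also collect the dates of symptom onset and diagnosis, and so know the exposure of interest.

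Data storage and analysis plans regression of baseline characteristics on diagnostic delay. If CRP or ASDAS-CRP is among those characteristics, timing error unrelated to delay would mainly cost precision. A lag or a selection that varies with delay would distort the association itself. An analysis plan cannot undo this from the study database, because omitted values are not there.

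**Working it through.** The plan gives no figure for this gap, so there is none to reproduce. The check is interval arithmetic on the stated limits, followed by one labelled illustration.

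**1. Gap between CRP and visit**

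Inputs, in months, with diagnosis at time 0:
- Visit time V: 0 to 6 (Study population), taking the baseline visit to coincide with recruitment (assumption).
- CRP time C: within 6 months of diagnosis (Baseline procedures), direction unstated.
- Gap = V − C. A positive gap means the CRP is older than the symptom scores.

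| Reading of the window | C | Smallest V − C | Largest V − C |
|---|---|---|---|
| Before diagnosis only | −6 to 0 | 0 − 0 = 0 | 6 − (−6) = 12 |
| After diagnosis only | 0 to 6 | 0 − 6 = −6 | 6 − 0 = 6 |
| Either side | −6 to 6 | 0 − 6 = −6 | 6 − (−6) = 12 |

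The CRP can thus be up to 12 months older than the questionnaires. The negative values (up to 6 months later) arise only if the record search is not cut off at the visit. For scale, the visit windows in the article are ±28 days (Table 1) or ±14 days (Follow-up procedures).

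**2. Which CRP feeds the score**

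The article does not say. The record-based CRP is the only baseline CRP it describes, and the Discussion stresses that the study has no specific procedures of its own. That this CRP enters ASDAS-CRP is therefore a well-supported inference, not a quotation.

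**3. Direction of the selection**

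- If normal values are judged unrelated to axSpA and dropped, recorded CRP is too high.
- If only raised values with another cause, such as infection, are dropped, recorded CRP is lowered.

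The wording allows both, so the sign is not determined.

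**4. Illustration of scale**

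The documents give neither the ASDAS weights nor a CRP distribution. Assume a weight of 0.579 on ln(CRP+1):

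Shift = 0.579 × [ln(CRP used + 1) − ln(CRP at visit + 1)]

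- Used 20, visit 5 mg/l: 0.579 × (ln 21 − ln 6) = 0.579 × 1.253 = +0.73.
- Used 5, visit 20 mg/l: −0.73.
- Equal values: 0.

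For this constructed pair the range is −0.73 to +0.73. It shows what one participant's score could do and does not estimate the average bias.

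**The case against.** The strongest reply is that this is a condensed article. Protocol version 3.0 and the supplementary material are not shown, and the choice of CRP for a derived score commonly sits in an analysis plan or eCRF guidance. That stands for the derivation rule. It does not cover the data-capture rule, which the article states outright and which determines which values are kept.

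Other points that stand:
- A routine CRP taken on or near the visit day can also qualify. The mismatch is permitted but need not occur in every participant.
- The relatedness filter may be meant only to remove rises caused by infection, which is a sensible aim.
- No mechanism is documented by which knowledge of the delay changes the judgement. The lack of blinding is a risk, not a demonstrated bias.
- The long-term outcomes named are work participation, quality of life and function. Most outcomes are patient reported, BASDAI is collected at every visit, and no analysis of ASDAS change is named.

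A reader might infer that baseline ASDAS is biased upwards and later improvement exaggerated, or that sites will pick the highest value on record. The documents support neither: the filter can act in both directions, and no highest-value rule appears anywhere. Nor does the bare clause on CRP/ESR at 24 months prove that a different rule applies there. It shows only that the article states none.

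**Conclusion.** The concern holds as a defect in a stated data-capture rule. Baseline CRP/ESR is anchored to diagnosis instead of the visit and passes through an unblinded, subjective filter, while the score it appears to feed is described as current. The permitted gap is up to 12 months before the visit, or up to 6 months after it under a forward window without a cut-off. This rests on the stated 6-month limits, on the baseline visit coinciding with recruitment, and on the inference that the recorded CRP is the one used in ASDAS-CRP.

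Neither the sign nor the size of any bias can be derived from the documents. The 0.73-unit shift is an illustration under an assumed weight and assumed CRP values. The matter should be corrected because it touches a baseline measure of disease activity that may be related to delay. It does not undermine the cohort or its patient-reported outcomes.

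**What to change.** 1. Record every available CRP and ESR with its sample date, whatever its level or presumed cause.
2. Flag intercurrent infection or another cause in a separate field instead of leaving the value out. The purpose of the present filter can then be served at analysis, openly and reversibly.
3. Derive ASDAS-CRP from the value nearest the visit within a prespecified window anchored to the visit, as imaging is already anchored to study entry. State the length of the window and whether values after the visit count.
4. Apply the same rule at the 24-month visit.
5. Where a b/tsDMARD was started between the CRP and the questionnaires, flag the score and examine it in a sensitivity analysis. Setting it to missing would remove participants according to treatment, which is likely to track severity.
6. Report BASDAI alongside ASDAS-CRP.

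The cost is eCRF guidance, a few fields and a derivation rule, with no extra blood test. Some more ASDAS-CRP values will be missing where no CRP falls inside the window. The article describes recruitment as ongoing, with a planned end in June 2026, so the rule can apply to participants still to be enrolled. For those already enrolled, sites would have to return to the records to restore omitted values.

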### Follow-up procedures

At 6-month intervals (months 6, 12, 18, 30 and 36) participants will be asked to complete electronic data collection sheets and questionnaires (Table 2) via e-mail or text message. These will collect data regarding disease activity and EMMs in addition to patient-reported outcome measures. Participants will be sent up to three electronic reminders via the Research Electronic Data Capture (REDCap) system to complete each visit. Each visit will have a window of 28 days (±14 days). Participants may request paper versions, if required.

At 24 months (Fig. 1), participants will be invited for a further in-person review to collect data on medication use related to axSpA, employment status, alcohol and smoking status and comorbidities. Participants will be examined for any extra-axial features of SpA and data from routinely performed MRIs, X-rays and CRP/ESR will be collected. Patient reported outcomes and questionnaire data will also be collected at this visit (Table 2).

### Events of special interest

Only relevant predefined events of special interest (pregnancy and development of EMMs) will be recorded on the electronic case report form (eCRF).

#### Pregnancy

Participants who have reported a pregnancy will be asked to complete a questionnaire within 6 months after the due date. This will collect information on the date of conception, previous pregnancies, pre-conception counselling, assisted conception, complications in pregnancy, gestation length, pregnancy outcome, complications in labour and delivery, postpartum complications and infections, breastfeeding and perinatal complications.

#### EMMs

The development of EMMs will be recorded by either the physician/researcher (month 24) or the participant (months 6, 12, 18, 30 and 36). These include a new diagnosis of psoriasis, uveitis and IBD.

### Data storage and analysis

Data will be recorded in a standardized eCRF to ensure uniformity across all participating clinical sites using REDCap software, created by Vanderbilt University (Nashville, TN, USA). Data will be collected, stored and processed in compliance with the General Data Protection Regulation and the Data Protection Act 2018. Statistical analysis will be performed by researchers and statisticians in the Leeds Teaching Hospitals Trust and University of Leeds and other co-investigators in participating centres. Initially, descriptive statistics will be used to describe the demographics of patients newly diagnosed with axSpA. Regression analysis and other statistical methods will be applied to determine the impact of diagnostic delay on baseline characteristics as appropriate. As longer-term data become available, analysis will evaluate the impact of diagnostic delay on comorbidities, work participation and functional outcomes, describing the natural history and impact of newly diagnosed axSpA and identifying potential predictors of poor long-term outcome and b/tsDMARD therapy use.

### Ethics approval and consent to participate

Ethical approval for the BAxSIC study was obtained from the Wales Research Ethics Committee 7 (22/WA/0311) in 2022. The BAxSIC study is sponsored by the Leeds Teaching Hospitals Trust (RR21/146198) and is adopted on the National Institute Health and Research (NIHR) musculoskeletal study portfolio (54230) being eligible for the NIHR Associate Principal Investigator Scheme. All participants provide informed, written consent to take part in the study. Ethical approval for same-day and remote consent has been granted. The BAxSIC protocol has undergone two amendments, with the latest version (3.0) dated 20 December 2023. Protocol amendments will be disseminated to each study site for reconsent and updating of participants.

### Trial oversight

The BAxSIC study is coordinated by a TMG that consists of a chief investigator, deputy chief investigator, co-investigators and study coordinator. The TMG will act as the Data Access Committee. Independent oversight of the study will be conducted by the Trial Steering Committee, expected to meet yearly and which will include a lay individual, lay clinician independent of the study research team and at least one patient representative. In addition, an External Advisory Committee of three international experts has been appointed to advise the study investigators on maximizing the usefulness of the inception cohort for research purposes and to align opportunities for data collection with international studies or potential collaborations.

